
#### Procedure

The intervention procedures are as follows: The CIE model uses an enablement officer from the research team who is an advanced health professional specializing in geriatric care and understands the philosophy and specific details of the model. The enablement officer facilitates the implementation of the model in each community-based eldercare centers by arranging a time to meet representatives of all participating providers to train and empower them. A coordinator team consisting of a GP from primary health care institution and a community staff is then set up in each center and coordinates participants’ community care by linking them with existing services. ^**{26a}**^The coordinator team contacts eligible individuals and discuss the project with them. Upon completion of their verbal consent, a multidisciplinary team involving a GP, a rehabilitation doctor, and a social worker conducts CGAs and develops care plans based on a set of guidelines. The proposed plans are then reviewed, modified, and confirmed by older residents and their family. Explicit attention is paid to the necessary support and guidance of the caregivers. The responsibilities and activities of the involved professionals are formalized in agreed plans. Thus, the coordinator team functions as an entry point through which older adults can access the expertise and services of all health and social care professionals and organizations. The coordinator team also supports the multidisciplinary team by arranging meetings and streamlining the necessary exchange of information. ^**{11b}**^A secondary line geriatric specialist is invited to join the interdisciplinary discussion if the needs are multiple or of a complex nature. A trial steering group in each community-based eldercare center consisting of two administrative staff from the center and the villagers’ committee is responsible for running the trial day-to-day and providing organizational support. They will meet leaders of the coordinator team and the multidisciplinary team once a month. There are no restrictions regarding concomitant care during the trial.

### Comparator {6b}

During the control period, usual care will be administered by staff from each CEC and primary healthcare station. Services provided by social workers are formalized in agreed protocols with the county government. Healthcare services provided by GPs are identical to the usual practices. While social workers generally do some assessments, neither CGA nor CBR tends to be conducted by the multidisciplinary team or in a systematic way. Consultations with the older residents and their caregivers during the implementation process are very limited. The execution of care delivery is left to the discretion of care staff of each CEC and primary healthcare station, following their existing practice patterns. Restrictions regarding concomitant care during the trial are not available either.

### Patient and public involvement

There were public and patient involvements in the design of the protocol.

### Outcomes {12}

The outcomes will be measured four times at (1) T0 (2 weeks, the end of preparation period), T1 (6 weeks; the end of observation period), T2 (28 weeks; 20 weeks after the beginning of the intervention), and T3 (48 weeks; the end of the intervention). Outcome data will be collected by external research assistants trained by the CIE research team (Table 1).

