**Methods:**

CIE is a prospective stepped-wedge cluster randomized trial conducted at 5 community eldercare centers in rural China. The multifaceted CIE intervention, guided by chronic care model and integrated care model, consists of five components: comprehensive geriatric assessment, individualized care planning, community-based rehabilitation, interdisciplinary case management, and care coordination. The intervention is rolled out in a staggered manner in these clusters of centers at an interval of 1 month. The primary outcomes include functional status, quality of life, and social support. Process evaluation will also be conducted. Generalized linear mixed model is employed for binary outcomes.

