## Methods

### Study design {8}

This study will adopt a multicenter, prospective, unidirectional randomized controlled trial using a stepped-wedge cluster design with repeated cross-sectional samples. Four phases will be sequentially rolled out over 48 weeks: preparation, control phase (standard care exposure), transition phase (intervention introduction), and intervention exposure (Fig. 1).

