### Statistical analysis {20a, 20b, 20c}

Data analysis will be performed using STATA 15. Baseline differences between clusters will be tested using Pearson’s chi-square statistic and ANOVA.

Statistical analysis is based on the Hussey and Hughes model for the analysis of cross-sectional SW-RCT designs [37]. Generalized linear mixed models (GLMM) will be used to determine the effect of the CIE model on the primary outcomes. Two random effects will be introduced, one at the cluster (eldercare centers) level and the other at the individual (frail older people) level. In addition to assessing the intervention effect, we will also investigate whether the time of intervention impacts the effectiveness of the intervention by adding an interaction term between time and intervention as a fixed effect. A secondary analysis will be conducted to adjust for baseline covariates to account for potential confounding effects. The same GLMM will be used to model the primary outcomes. Estimates of difference and 95% CIs will be calculated.

Qualitative data from interviews or focus groups will be analyzed using content analysis, document analysis, etc.

The analysis is based on intention to treat (ITT) principle. Multivariable normal models will be used for imputation of missing values to enable ITT analysis. A *P* value < 0.05 will be considered statistically significant.

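### On the stated calendar every site crosses over between T1 and T2, so the planned on/off intervention effect is aliased with calendar period and the stated 80% power does not apply to it

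*Protocol article*

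**What the plan says.** Under Outcomes {12} the protocol states that "The outcomes will be measured four times": at "T0 (2 weeks, the end of preparation period"), and then at "T1 (6 weeks; the end of observation period), T2 (28 weeks; 20 weeks after the beginning of the intervention), and T3 (48 weeks"), the last being the end of the intervention.

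The Abstract describes five clusters ("CIE is a prospective stepped-wedge cluster randomized trial conducted at 5 community eldercare centers in rural China") with the intervention "rolled out in a staggered manner in these clusters of centers at an interval of 1 month". Study design {8} gives the total length: "Four phases will be sequentially rolled out over 48 weeks".

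Randomization and blinding keeps all sites on usual care for the first 6 weeks. It gives each site a 2-week transition before it crosses, and places that transition in the last 2 weeks before the next step. The same section also speaks of five sites starting in the first step, although the trial has only five.

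Statistical analysis states: "Statistical analysis is based on the Hussey and Hughes model for the analysis of cross-sectional SW-RCT designs". It adds a fixed-effect interaction between time and intervention. Sample size {14} claims 80% power at 5% two-sided for quality of life, with ICC 0.01 and a minimum cluster size of 76.

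**The concern.** A stepped-wedge trial separates the intervention from calendar time by comparing, at the same time, sites that have crossed with sites that have not. That requires outcome data during the roll-out. Here the gap between T1 and T2 is 28 − 6 = 22 weeks, and all the crossovers appear to fall inside it.

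If so, the planned on/off contrast sets weeks 2 and 6 against weeks 28 and 48 in every site alike. Ageing, season and the county's eldercare policy changes (described in the Discussion) would pass into the estimate undiminished. The Discussion proposes to handle secular trends partly by adjusting for baseline covariates. Such covariates cannot separate a calendar trend from an exposure that switches in every site between the same two assessments.

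**Working it through.** **1. First crossover.** Outcomes {12}: 28 − 20 = week 8. Randomization and blinding agrees: 6 weeks of usual care + 2 weeks of transition = week 8, and 6 + 2 + 20 = 28. The plan's own T2 figure is reproduced.

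**2. Later crossovers.** Site k crosses at 8 + (k − 1) × step.
- 4-week month: weeks 8, 12, 16, 20, 24.
- 31-day month (4.43 weeks): weeks 8, 12.4, 16.9, 21.3, 25.7.
- A further 2 weeks added once at the start: last crossover at week 26.0 to 27.7, still before week 28.

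The last site is still in control at week 28 only if the step exceeds (28 − 8)/4 = 5 weeks.

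**3. Exposed sites at T0, T1, T2, T3:** 0, 0, 5, 5. The intervention column equals the T2 indicator plus the T3 indicator. With site and categorical period effects there are 9 columns but rank 8, the same rank as without the intervention term.

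**4. Variance of the period-adjusted effect.** For I clusters, T occasions and exposure X:

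Var = Iσ²(σ² + Tτ²) / [(I·S − W)σ² + (U² + I·T·S − T·W − I·V)τ²]

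Here U = ΣX, S = ΣX², W is the sum over occasions of squared column totals, and V is the sum over sites of squared row totals. Total variance is set to 1, ICC 0.01 gives τ² = 0.01, and 76 per site per occasion gives σ² = 0.99/76 = 0.01303. Samples are cross-sectional. For I = 5 and T = 4 the numerator is 5 × 0.01303 × 0.05303 = 0.003454. The detectable effect at 80% power and two-sided 5% is (1.960 + 0.842) × SE.

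| Exposure | U | S | W | V | Denominator | SE | Detectable |
|---|---|---|---|---|---|---|---|
| 0, 0, 5, 5 (as planned) | 10 | 10 | 50 | 20 | 0σ² + 0τ² = 0 | infinite | none |
| 0, 2, 3, 5 | 10 | 10 | 38 | 24 | 12σ² + 28τ² = 0.4363 | 0.089 | 0.25 SD |
| 0, 0, 4, 5 (steps of about 6 weeks) | 9 | 9 | 41 | 17 | 4σ² + 12τ² = 0.1721 | 0.142 | 0.40 SD |

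For comparison, assessing in all six wedge periods gives SE 0.070 and a detectable effect of 0.20 SD.

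**5. Time on intervention.** With 4-week steps, sites have 20, 16, 12, 8 and 4 weeks of exposure at T2, and 40, 36, 32, 28 and 24 at T3. They differ within an assessment, and the order is randomised. In units of 20 weeks, U = 11, S = 15.4, W = 73 and V = 25.8. The denominator is 4σ² + 8τ² = 0.1321, so Var = 0.003454/0.1321 = 0.0261 and SE = 0.16 SD per 20 weeks (0.15 with calendar months). The detectable linear effect is 2.80 × 0.15 to 2.80 × 0.16, or about 0.42 to 0.45 SD per 20 weeks. Adding this term leaves the on/off term aliased.

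**6. Site-specific clock.** If T1 and T2 are counted from each site's own schedule, the latest control assessment is at 6 + 16 = week 22 (23.7 with 31-day months) and the earliest intervention assessment at week 28. No calendar time contains both conditions, and the matrix is still rank-deficient.

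**The case against.** A reader might infer that the randomisation contributes nothing and that no intervention effect of any kind can be estimated. The documents do not support that. Step 5 shows that the randomised order sets time on intervention, so a linear exposure-duration effect is identified with categorical periods. It is imprecise and rests on the linear form, but it is not a before-after contrast.

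A reader might also infer that the planned time-by-intervention interaction is lost altogether. That depends on what time means in Statistical analysis. Read as calendar period, the interaction is aliased. Read as time on intervention, its slope is estimable, although the on/off main effect is not.

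The crossover weeks are reconstructed, since Figure 1 is not shown. If the 2-week transition were added to every interval, steps would be about 6 weeks and the last crossover about week 32. One site would then be in control at T2 and the on/off effect would be estimable (SE 0.14). That reading conflicts with the 1-month interval in the Abstract and with Randomization and blinding, which places the transition inside the interval. The effect would also depend on a single control site at one assessment.

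A site-specific clock cannot be dismissed on duration. With T2 at each site's own 20 weeks (weeks 28 to 44) and T3 at a common week 48, it fits the 48 weeks. Later sites' T1 would then come after the first crossover. The confounding with period remains, as step 6 shows.

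Finally, the literal statement that five sites start in the first step would remove the stagger. All sites would then have equal exposure at each assessment, and the time-on-intervention effect would be lost too.

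**Conclusion.** The point holds for the on/off effect. On the stated schedule, exposure is 0, 0, 5, 5 of 5 sites for any step up to 5 weeks, so the on/off effect and its interaction with calendar period are not identified in the Hussey and Hughes model. The stated 80% power does not apply to that effect. Dropping the period terms, or imposing a linear trend across weeks 2, 6, 28 and 48, would yield a number. That number would be a before-after estimate resting on an untestable trend assumption; the correlation of exposure with linear time across those four weeks is 0.92.

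What remains identified is a linear effect of time on intervention, with SE about 0.15 to 0.16 SD per 20 weeks. The conclusion assumes categorical periods, one site per step and 1-month steps. The SEs further assume 76 per site per assessment, ICC 0.01 and cross-sectional sampling. The protocol states no effect size or SD for quality of life, so these detectable effects cannot be set against its planning target.

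**What to change.** First reconcile the Abstract (1-month interval), Outcomes {12} (assessment weeks), Randomization and blinding (transition, and five sites in the first step) and Statistical analysis. State each site's crossover week, and whether the assessment weeks run on one common clock.

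**If dates can still move:** keep four assessments, but place two inside the roll-out, with all five sites assessed in the same week while some are exposed and others are not. Exclude sites in their 2-week transition or code them separately. Fit categorical period effects and restate the detectable effect: about 0.25 SD at 0, 2, 3, 5 exposed sites, before allowing for transition sites and short exposure. With 4-week steps, weeks 12 to 14 and 16 to 18 avoid all transitions and give 2 and 3 exposed sites, but the newest site then has at most 2 weeks of exposure.

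**If dates cannot move:** Trial status planned recruitment for October to November 2022 and the article appeared in May 2023, so T1 may already have passed. In that case, withdraw the 80% power claim for the on/off effect and report that effect as a before-after estimate not separable from calendar time. Use the randomised order only for a pre-specified time-on-intervention analysis with categorical periods.

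**Cost:** no extra assessments, but short exposure at the mid-roll-out assessments and a less favourable stated detectable effect. The fallback costs the headline stepped-wedge claim for the on/off effect.

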#### Primary outcomes

*Frailty*: The Chinese version of Groningen Frailty Indicator (GFI) will be used to measure frailty with a cut-off point of 3. It is composed of 15 items and divided into four domains. The total score ranged from 0 to 15 with each item having a score of 0 or 1. The GFI demonstrates good reliability with Cronbach’s alpha coefficient of 0.64 and acceptable construct and criterion validity as described by Tian et al. [27]. *Quality of life*: The Chinese version of the 36-item Short Form Health Survey (SF-36) is administered which is comparable to the original scale with respect to reliability, convergent, and discriminant validity tests. It generates scores across eight dimensions of health that can be summarized into Physical Components Summary (PCS) and Mental Components Summary (MCS). The SF-36 has proved useful in monitoring population health outcomes in clinical practice, and evaluating treatment effects [28].*Mental well-being*: Depressive symptoms will be measured using the Center for Epidemiological Studies Depression Scale (CES-D). The CES-D consists of 16 negative affect and 4 positive affect items. Each item is accompanied by a standard 4-point Likert scale of potential responses. Higher scores on the CES-D indicate more depressive symptoms. The Chinese version of this scale has been validated and extensively used in community-based population [29]. Seven-item scale for General Anxiety Disorder (GAD-7) will serve as the self-rated measure of anxiety. The GAD-7 score is calculated by assigning scores of 0, 1, 2, and 3 to seven questions respectively. Scores of 5, 10, and 15 were taken as the cut-off points for “mild,” “moderate,” and “severe” anxiety, respectively. This instrument showed good reliability and validity in Chinese population [30].*Social support*: Likert scale is composed of three subscales that can be classified into informational support, emotional support, and household activity support. Its reliability and validity have been confirmed in a previous study [31].

#### Secondary outcomes

*Patient-reported measurement of the shared decision-making process*: Patient experience of shared decision-making process will be measured using the CollaboRATE tool. The tool will assess the extent to which each of three core shared decision-making tasks (or dimensions) are present in a clinical encounter: (1) explanation of the health issue, (2) elicitation of patient preferences, and (3) integration of patient preferences. Each question will be scored on a 5-point Likert scale, with responses of 0 (no effort was made), 1 (a little effort was made), 2 (some effort was made), 3 (a lot of effort was made), and 4 (every effort was made) [32].  *Collaborative function of an interprofessional team*: The level of collaborative practice among interprofessional team will be measured by The Collaborative Practice Assessment Tool (CPAT). The CPAT survey includes 56 items across nine domains identifying strengths and weaknesses in their collaborative practice. CPAT is a valid and reliable tool for measuring healthcare team members’ perceptions of working collaboratively [33].

### Sample size {14}

The sample size for this stepped-wedge controlled randomized trial (SW-CRT) is calculated to detect minimal significant effects on the variable of quality of life: accepting an alpha risk of 0.05 and a beta risk of 0.20 in a bilateral contrast, referring the study of Ana.et al. [34]. Assuming the intracluster correlation coefficient (ICC) to be 0.01 based on Boorsma et al.’s study [35] and correlation coefficient to be 0.25 based on the ratio between the ICC and the correlation coefficient used in the study of Muntinga et al. [36], a minimum cluster size of 76 individuals is required to detect the expected intervention effect with 80% power at the 5% significance level.

Based on our earlier survey study on community-dwelling older people and available data on the characteristics of long-term care residents [17], we expect a 20% loss to follow-up due to mortality, impossibility, or unwillingness to participate further, 16 more individuals would be required, the resultant sample size is determinate in 92 individuals per cluster per period.

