### Study sites and participants {10}

Five CECs were purposively selected based on geographic location and representativeness of the frailty in Lishui county.

Study sites were purposively selected in collaboration with villagers committee and Bureau of Civil Affairs according to the following criteria: (1) sites where CBR services were delivered by the tertiary hospital; (2) at least 20,000 visits per year altogether in selected CECs. Based on previous data in the county [17], we assumed each site may be able to see on average 40 frail older people and they are present at least 100 days per year (eight per month); (3) routine eldercare available onsite; (4) no previous introduction of interventions/organizations for integration or increasing services, apart from CIE that is considered as standard-of-care throughout the whole study period.

Study participants consists of all the adults aged 65 or older who are present for care in the selected CECs and agree to participate during the study period. Inclusion criteria are as follows: (1) with household registration in Lishui county; (2) not planning to move away from Lishui county in the prospective follow-up of the study; (3) Chinese version of Mini-Mental State Examination score ≥ 20; (4) written informed consent to participate in the study. For those who had difficulty in writing, informed consent was obtained from their spouses/children. The oral informed consent was recorded when the older people or their family members cannot write. Exclusion criteria are as follows: (1) on a waiting list for a nursing home; (2) with a terminal medical condition; (3) older adults who have psychiatric disorders or other illnesses that require hospitalization; (4) older adults who are currently receiving specialist geriatrician intervention and/or care coordination.

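### The 20% loss allowance gives 92 per cluster per period where the plan's own inputs need 95, and neither figure is reconciled with the roughly 40 frail people assumed per centre

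*Protocol article*

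**What the plan says.** All references are to the protocol article.

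- **Sample size {14}.** The calculation is "calculated to detect minimal significant effects on the variable of quality of life", two-sided at 5% with 80% power. No numerical effect or SD is given. It assumes an ICC of 0.01 and a second correlation of 0.25, and states that "a minimum cluster size of 76 individuals is required to detect the expected intervention effect with 80% power". On attrition it says "we expect a 20% loss to follow-up due to mortality, impossibility, or unwillingness to participate further", and concludes that "16 more individuals would be required, the resultant sample size is determinate in 92 individuals per cluster per period".
- **Study sites and participants {10}.** Within a site-selection criterion on visit volume (at least 20,000 a year over the chosen centres), the text says "we assumed each site may be able to see on average 40 frail older people", each attending at least 100 days a year. Eligibility covers attenders aged 65 or over. None of the four inclusion criteria is a frailty score.
- **Participant recruitment {15}.** Participants are chosen from a county roster of residents over 65.
- **Study design {8}** describes repeated cross-sections, whereas Sample size {14} allows for loss to follow-up.

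**The concern.** Two things do not fit.

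First, an allowance for loss has to leave the required number after the loss has occurred. Adding 20% of 76 does not do that, because the 20% is lost from the larger enrolled number.

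Second, the title, the objective and the individual-level random effect in Statistical analysis {20a, 20b, 20c} all concern frail older people. Yet the only count of frail people per centre is 40, and the requirement is 92 per cluster per period. Either the sample will include many people outside that frail count, or the number analysed will be well below the one that supports the stated power. The article does not say which.

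**Working it through.** **1. The loss allowance**

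Inputs from Sample size {14}: 76 evaluable per cluster, 20% loss, 92 stated.

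- Reproducing the plan's figure: 76 × (1 + 0.20) = 91.2, rounded up to 92 (76 + 16).
- Check: 92 × (1 − 0.20) = 73.6 evaluable, below 76.
- Loss that 92 can absorb: (92 − 76)/92 = 16/92 = 17.4%.
- Correct inflation: 76/(1 − 0.20) = 95, that is 19 more rather than 16. Check: 95 × 0.80 = 76.
- Over five centres: 95 × 5 = 475 against 92 × 5 = 460, a difference of 15 per period.

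**2. What the 40 counts**

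5 centres × 40 people × 100 days = 20,000, which is exactly the visit threshold. So 40 is a number of persons per centre, not of visits.

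- 92/40 = 2.3, and even 76/40 = 1.9.
- Five centres: 40 × 5 = 200 against 460.
- Gap per centre: 92 − 40 = 52, or 52/92 = 57%.
- If 20% of 40 are lost: 40 × 0.80 = 32 evaluable.

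**3. Effect on power**

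The 76 cannot be reproduced without an effect size and SD. The effect δ was therefore fixed at whatever 76 per cluster-period detects with 80% power, and power was recomputed at other sizes m:

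δ = (1.960 + 0.842) × SE(76); power(m) = Φ(δ/SE(m) − 1.960)

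SE(m) comes from the generalised least squares variance of a stepped-wedge model (Hussey and Hughes, with extensions for cluster and individual autocorrelation).

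The following are assumptions, not protocol statements: five sequences, 6 or 12 periods, and a normal approximation. The article does not say which autocorrelation its 0.25 is, so both readings were run. ICC values above the stated 0.01 are sensitivity checks. Selected results:

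| Periods | ICC | Cluster autocorr. | Individual autocorr. | m = 73.6 | m = 40 | m = 32 |
|---|---|---|---|---|---|---|
| 6 | 0.01 | 1 | 0 | 78.8% | 55.7% | 48.0% |
| 6 | 0.01 | 1 | 0.25 | 78.8% | 54.2% | 46.0% |
| 6 | 0.01 | 0.25 | 0 | 79.3% | 63.1% | 56.3% |
| 12 | 0.01 | 1 | 0 | 78.8% | 53.6% | 45.3% |
| 12 | 0.01 | 1 | 0.25 | 78.7% | 53.2% | 44.7% |
| 12 | 0.01 | 0.25 | 0 | 79.2% | 62.0% | 55.0% |
| 12 | 0.25 | 1 | 0 | 78.7% | 52.9% | 44.4% |

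As a check that needs no design, take SE proportional to 1/√m. Power is then Φ(2.802 × √(m/76) − 1.960), which is 78.7% at 73.6, 52.9% at 40 and 44.4% at 32. This agrees with the low end of each column.

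Over all runs the ranges are 78.7–79.3% at 73.6, about 53–63% at 40, and about 44–56% at 32.

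**The case against.** The tempting stronger reading is that the centres cannot supply the sample, so 80% power is not delivered. The documents do not support it.

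- Eligibility covers attenders aged 65 or over and sets no frailty threshold. The frailty indicator and its cut-off appear under Outcomes {12}, not as an entry test, and recruitment works from a roster of over-65s. Nothing written caps enrolment at 40.
- The 40 stands in a site-selection criterion, in hedged wording and tied to a minimum visit volume. It is not a recruitment forecast. The number of eligible people aged 65 or over at each centre is not given, so 92 is not shown to be out of reach.
- The power figures at 40 and 32 rest on an assumed layout. Outcomes {12} lists four measurement times, the design figure is not available here, and no effect size or SD is stated. Absolute power can be neither confirmed nor refuted.
- The inflation slip amounts to three people per cluster per period and about one point of power.

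All of this stands, and it limits the point to a small correction and a request to reconcile. It does not remove either. The arithmetic is wrong whatever the recruitment pool. Wide eligibility answers the headcount question only by admitting people beyond the assumed frail count, which the article does not acknowledge when it describes its population as frail. Nor does the visit threshold help: 40 people per centre at the stated attendance meet it in full, so it is no evidence that 92 attend.

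**Conclusion.** Two conclusions, of different weight.

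**Certain but small.** By the plan's own inputs, 92 should be 95 per cluster per period. As stated, 92 covers 17.4% loss, or gives about 79% power at 20% loss.

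**Unreconciled, and potentially large.** A requirement of 92 per cluster per period stands beside an assumption of about 40 frail people per centre, with no explanation. Power of about 53–63% (40 analysed) or 44–56% (32 analysed) follows only if enrolment or the target analysis is limited to those 40. It also holds δ at what 76 detects with 80% power and assumes a five-sequence wedge. If the sample is not so limited, the stated size is not refuted, and the question becomes how many of those analysed are frail.

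Whether 475 would be a total for one cohort or a number for each period cannot be settled from the text: repeated cross-sections point one way and loss to follow-up the other. New individuals in each period would widen the gap with 40, not close it.

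**What to change.** 1. In Sample size {14}, replace 92 with 95 per cluster per period (19 added, not 16). Alternatively, keep 92 and state that it tolerates about 17% loss, or gives about 79% power at 20% loss. The first option means 15 more people per period over five centres. The second needs only a change of wording.
2. State whether enrolment or the target analysis is limited to frail people.
   - If it is, restate power or the detectable effect at the number the centres can supply (40 each, about 32 after 20% loss, on the protocol's own assumption), using the effect size and SD behind the 76. The stated power will then be less favourable.
   - If it is not, replace the 40 with the centre or roster count that supports 95, and say that the sample includes people who are not frail.
3. Say whether the same people are followed or new ones are sampled each period, so that 95 per cluster per period can be turned into a total.

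Items 2 and 3 need text and, at most, a roster count and a rerun of the existing calculation.
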